### Site recruitment

An invitation was circulated to Aboriginal-Controlled Community Health Organizations [ACCHO] in the Northern Territory to attend an information workshop at the Alice Springs Hospital. Following this, an expression of interest was sought from attendees. A discussion paper was circulated for internal discussions within the health service to the three health services that formally expressed an interest in the project. Once health service board approval had been obtained, a formal letter of support from the health service for the TEAMSnet study was sought and Memoranda of Understanding and service agreements were executed between partner sites and the administering institutions, the Universities of Melbourne and Sydney. Ethics applications were submitted by investigators to the Central Australian and Menzies School of Health Research Human Research Ethics Committees. Recruitment commenced once written ethics approval had been obtained.

### Participant eligibility

#### Inclusion criteria

Participants must be clients of the partner health services who are aged 18 or over; can provide informed consent; can successfully undergo retinal imaging; are willing to undertake surveys and provide relevant clinical information; and are willing to consult their doctor on at least two occasions over the following 18 months.

#### Exclusion criteria

Clients of the partner health services are ineligible if they been clients for less than six months prior to enrollment or have had diabetic retinopathy treatment.

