## Methods/Design

### Study design

This is a pre-post study of technology-facilitated management of diabetes, CVD, and diabetic retinopathy. We plan to enrol 600 adults (age ≥18 years) with clinically-diagnosed diabetes from three remote Northern Territory Aboriginal-controlled health services — Central Australian Aboriginal Congress [CAAC] in Alice Springs, Miwatj Health Aboriginal Corporation [Miwatj] that incorporates the four clinics at Nhulunbuy, Galiwin’ku/Elcho Island, Yirrkala, Gunyangara/Ski Beach in East Arnhem Land and Wurli-Wurlinjang Health Service [Wurli] in Katherine. Recruitment and intervention are anticipated to occur over a 3-year period. Participants will receive retinal imaging, diabetic retinopathy screening, including diabetes education, at baseline, followed by lifestyle assessment six months later, including self-management support. An electronic CVD and diabetes decision support tool that includes an Indigenous-specific CVD risk calculator, based on best-practice as generally defined by guidelines in the current Standard Treatment Manual of the Central Australian Rural Practitioner’s Association [CARPA], will be developed in conjunction with a clinical working group and used to generate a clinical recommendations report to assist clinicians with evidence-based management of CVD, diabetes and diabetic retinopathy approximately 6–18 months after baseline. Mobile tablet technology based on clinical input and feedback will be developed to support clinical staff and participants with engagement in diabetes management and self-management, respectively.

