Our second objective is to improve the timely exchange of relevant health information and the communication between a patient’s health care providers. CDMP facilitates this through use of a unique practitioner access code that enables a specialist medical practitioner, such as an optometrist or ophthalmologist, to view only relevant patient data, including reports.
*Improve engagement of patients in self-care, particularly adherence to clinical visits*
Our third objective is to improve engagement of patients in self-care. GRI retinal imaging will provide both a powerful education and retinopathy assessment opportunity. In addition, a third technology, (3) a custom-built e-mobile health device in the form of a tablet with viewable clinical data, GRI images and educational content, developed with clinical and Aboriginal Health Worker input, will facilitate health worker communication with patients between medical consultations and is aimed at improving relationships and engaging patients in self-care. A fourth application, (4) a suite of lifestyle surveys and a related reporting template based on CARPA recommendations for smoking, nutrition, alcohol, physical activity and emotional well-being [SNAPE] has been developed and is accessible via CDMP in a clinical setting or via the mobile tablet application anywhere. This is designed to be both a patient engagement and clinical management tool that facilitates the measurement, goal-setting and monitoring of important lifestyle risk factors for CVD, diabetes and diabetic retinopathy. All three telehealth reports, EDS, GRI and SNAPE, will be accessible via either the EHR [Communicare] or CDMP.

Apart from the development and implementation of the four technologies, the primary outcome includes improved adherence to clinical care, such as eyecare visits. Secondary outcomes include reduction in hospitalizations and cost-efficacy of the suite of technologies, both individually and collectively.

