### Data collection and outcome measures

Demographic data (including age, gender, postcode, contact details) and self-report measures are obtained from each participant at baseline and/or at the 6-month survey administration visit. Pre- and post-study clinical data such as blood and urine biochemistry, blood pressure and anthropometric measures including height and weight are also collected. Pre- and post-study health care resource utilization is captured through EHR records and includes information on hospitalizations and eye-care consultations.

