#### Pre-study data

Site partners will collaborate to audit the Communicare EHR for each participant in order to obtain the required pre-study data i.e. the data that correspond with post-study data relating to CVD, diabetes or diabetic retinopathy risk and outcomes and each participant’s use of health services, such as eye-care consultations and hospitalizations.

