## Data analysis

Investigators and their supporting statistics departments will conduct data analysis. Site differences will be analysed. Analyses will provide important descriptive data, such as prevalence rates and lifestyle data, proportion treated to target for CVD, diabetes and diabetic retinopathy risk factors and predictors of diabetic retinopathy and CVD outcomes. Analysis of covariance (ANCOVA) will be used to compare differences between groups. To assess confounding, covariates will include age, gender, and established and emerging risk factors for CVD, diabetes and diabetic retinopathy, as appropriate. Non-parametric statistics will be used when assumptions for parametric methods are violated. All tests will be conducted using an alpha level of 0.05 and 95% confidence intervals will be reported.

Complete case analysis and, where reasonable, multiple imputation will be employed for the management of missing data. Missing data may occur due to drop-out, missed assessments or item non-response. With knowledge of the missing data mechanism, all available information can be used. One approach will be to use the multilevel model, a full-likelihood method that allows for a response to be missing at random, where missingness depends only on observed data and not on unobserved data. Another strategy involves imputing missing values by multiple imputation procedures.

The proposed economic evaluation aims to include pre- and post-study resource utilization costs for both the costs and consequences and a cost consequence analysis (CCA). Standard unit costs i.e. Australian Medicare Benefits Schedule will be applied to the resource-use data. Costs will be presented in total and disaggregated forms, such as those from different sectors — the health sector, patients and government.

Of the recruitment target of 600 Indigenous Australians with diabetes, to date 576 participants have been recruited and undergone retinal imaging for diabetic retinopathy screening.

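### Excluding previously treated clients sets retinopathy-treatment visits and costs to zero before enrolment, which biases that component of the pre-post eye-care and cost comparison upward

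*Protocol article*

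**What the plan says.** Study design in the protocol article describes one group compared with itself: "This is a pre-post study of technology-facilitated management of diabetes, CVD, and diabetic retinopathy". No concurrent control is described.

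Under Exclusion criteria, clients are ineligible if they "have had diabetic retinopathy treatment". No look-back period limits this.

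Three places set up the comparison:

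- Pre-study data: the electronic health record is audited for "each participant’s use of health services, such as eye-care consultations and hospitalizations".
- Data collection and outcome measures: "Pre- and post-study health care resource utilization is captured through EHR records and includes information on hospitalizations and eye-care consultations".
- Data analysis: "The proposed economic evaluation aims to include pre- and post-study resource utilization costs for both the costs and consequences", within a cost consequence analysis.

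Eye care also touches the primary outcome. Study aims and objectives says that "the primary outcome includes improved adherence to clinical care, such as eyecare visits", and lists cost-efficacy among the secondary outcomes.

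**The concern.** Anyone treated for retinopathy before enrolment is not in the study, so no participant can contribute a treatment visit or a treatment cost to the pre-study window, however long that window is. After enrolment nothing bars treatment, and a referral protocol follows the baseline imaging. One class of events is thus impossible in one window and possible in the other.

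With a control group, the same asymmetry would appear in both arms and cancel. Here nothing offsets it. Age, gender and risk factors as covariates cannot restore events that eligibility removed. What is at stake is the reading of two results: more eye-care consultations could be taken as better engagement, and higher eye-care cost as a cost of telehealth, when part of each comes from the entry criterion.

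**Working it through.** The plan states no figure to reproduce. The check has a logical step and an illustration of size.

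**Logic.** For each participant, eye-care use is the sum of treatment visits and other visits. Eligibility fixes the pre-study treatment part at 0. The expected change is therefore (post treatment visits) + (change in other visits). The first term cannot be negative, and with no intervention effect it is positive whenever anyone reaches treatment after enrolment. The second term can have either sign. Costs follow the same decomposition.

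**Inputs for the size.** Only the post-study length has a basis in the text: 1.5 years, from the inclusion criterion that participants be "willing to consult their doctor on at least two occasions over the following 18 months". The rest are assumptions:

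- constant hazard of first treatment h = 1%, 2% or 4% per year, the same with or without telehealth;
- v = 4 or 8 further treatment visits per year once treatment has started;
- r = 0.5 or 1.0 routine eye visits per year in both windows;
- a pre-study window of equal length. The article states no length. If use is expressed per year, the length drops out, because pre-study treatment is zero in any window.

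**Formulas.**

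- Share first treated within 1.5 years: P = 1 − exp(−1.5h).
- Mean treated time per participant: E = 1.5 − P/h.
- Mean treatment visits per participant: P + vE (one visit at the start, then v per year).
- Relative rise in mean visits: (P + vE) / (1.5r).
- Rise in the share with at least one eye visit: P × exp(−1.5r), since treatment adds to this share only among people with no routine visit.

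**Numbers.** For h = 1%: P = 0.01489 and E = 0.01119. With v = 4, P + vE = 0.0597, and 0.0597/0.75 = 8.0%. With v = 8, it is 0.1044, and 0.1044/0.75 = 13.9%.

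| h per year | P | E | P + vE (v = 4; 8) | Rise, r = 0.5 | Rise, r = 1.0 | Any-visit share, r = 0.5; 1.0 |
|---|---|---|---|---|---|---|
| 1% | 0.01489 | 0.01119 | 0.0597; 0.1044 | 8.0–13.9% | 4.0–7.0% | +0.70; +0.33 points |
| 2% | 0.02955 | 0.02228 | 0.1187; 0.2078 | 15.8–27.7% | 7.9–13.9% | +1.40; +0.66 points |
| 4% | 0.05824 | 0.04411 | 0.2347; 0.4111 | 31.3–54.8% | 15.6–27.4% | +2.75; +1.30 points |

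A simulation of 1,000,000 persons per scenario under the same assumptions gave rises of 8.3% to 54.5% at r = 0.5 and 3.9% to 27.3% at r = 1.0, in agreement within simulation error.

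In people: among 490 participants (the minimum in the Sample Size section), 490 × 0.01489 = 7.3 would be newly treated at 1% per year and 490 × 0.02955 = 14.5 at 2%, against 0 before.

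**Two less pessimistic variants.** If routine visits stop once treatment starts, the numerator becomes P + vE − rE, and the overall range moves from 4.0–54.8% to 3.2–51.9%. If each treated person has only 2 treatment visits in all, the numerator is 2P, and the range is 2.0% (h = 1%, r = 1.0) to 15.5% (h = 4%, r = 0.5).

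**The case against.** *The primary outcome is adherence, not a visit count.* This stands. The abstract and the Sample Size section speak of adherence, and the table shows that a yes/no measure hardly moves. If adherence is attended over scheduled visits, treatment appointments enter both numerator and denominator, and the direction of any bias is not determined. Because eye-care visits are the named example, a reader might infer that the primary outcome is materially inflated. The documents do not support that.

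*Total use need not rise.* This also stands. Only the treatment component is zero by selection. Examinations and reviews can occur in both windows and may fall. A reader might infer that eye-care use and cost must increase after enrolment; the eligibility rule does not imply it.

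*The size is unanchored.* Correct. Hazard, visit frequencies and pre-study length are all assumed, and the top of the range needs the highest hazard, the highest treatment frequency and the lowest routine rate together. Adding treatment to unchanged routine visits also pushes the figures up, though the substitution variant shows that this matters little.

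*A condensed article need not define consultation subtypes, and costs are already to be disaggregated.* Partly right. The absence of a coding scheme is not the fault. The point rests on two stated features, the exclusion and the pre-post comparison. The disaggregation given as an example is by sector, which does not separate treatment from screening.

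*Treatment after screening is an intended effect.* This is the strongest objection. Baseline imaging is meant to detect retinopathy in time and leads to referral, so some later treatment is a real consequence and a real cost of the intervention. Removing it from the only comparison would exchange one bias for another. It does not rescue the unadjusted comparison, because an uncontrolled design cannot separate prompted treatment from treatment that would have happened anyway.

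**Conclusion.** The concern holds in limited form. The exclusion makes retinopathy-treatment visits and costs zero before enrolment, and the uncontrolled comparison of eye-care counts and resource costs carries an upward bias in that component. The direction for the component follows from the text alone. The size does not: about 4% to 55% of mean eye visits in the main illustration, and as little as 2% if treatment involves few visits, all on assumed inputs. No cost figure can be given, because the article states no unit costs or treatment frequencies. The point concerns the interpretation of the count and cost results; it does not show that the primary adherence result is invalid.

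**What to change.** Leave eligibility and sample size alone; the article reports 576 of 600 participants already recruited. In the analysis:

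1. Keep the pre-post comparison of all eye-care consultations and all costs.
2. Beside it, present the same comparison without retinopathy-treatment visits and their costs.
3. Report post-study treatment visits and costs separately, as description and not as a change from pre-study.
4. State that the treatment component of the pre-post change cannot be attributed to the intervention, because eligibility sets its pre-study value to zero.

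The cost is small: each eye-care consultation must be coded as treatment or non-treatment in the record audit already planned. The version without treatment omits treatment that screening genuinely prompted, which is why both versions should be shown.

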### Sample recruitment

Both community-based and direct recruitment strategies are being used to recruit study participants. These include; flyers in medical waiting and consulting rooms, and contact with potential referral sources, for example, general practitioners, chronic care team members — podiatrist, dietitian, cardiac nurse, renal nurse, diabetes educator, text and letter invitations.

Prospective participants express their interest to the study co-ordinator at a face-to face meeting during which the individual is screened. If the individual meets the inclusion criteria, they are consented to the study (consent form signed after patient information sheet discussed) and diabetic retinopathy screening is performed (baseline visit) in order to reduce the time burden on participants and improve compliance with the study protocol.

### Study procedure

#### TEAMSnet telehealth protocols

Baseline visit — Retinal imaging-based diabetic retinopathy screeningImaging of participants by TEAMSnet trained clinic staff aims to provide a valuable patient education and engagement opportunity in addition to facilitating the timely detection of diabetic retinopathy.Our diabetic retinopathy screening method is based on a protocol developed in collaboration with the Joslin Diabetes Centre in the USA. Key features are — (1) Digital Imaging and Communications in Medicine (DICOM) compliant images from digital non-mydriatic retinal fundus cameras are cached or transmitted over the internet using Transport Layer Security [TLS] encryption [based on connectivity] via the GRI application to a remote grader. (2) Grading and reporting to Communicare at the originating site is completed within two working days of the grading centre receiving the imaging studies that can be viewed as an active work list on the grader’s computer system. (3) Images can be viewed anytime, anywhere in the web-based CDMP application by clinic-authorized personnel. Optometrists, ophthalmologists, primary care doctors, endocrinologists, nurses, health workers and retinal imagers will be provided with filtered levels of information via a unique access code.The main elements of the retinal imaging protocol are —History — Patient demographic data are entered. Presenting vision is recorded [pinhole if below 6/6 when possible], either unaided or aided by spectacles. If presenting vision is unaided, but patient has distance vision spectacles, then acuity with spectacles is also recorded. Date of last eye exam or any significant ocular history [surgery, trauma] is noted electronically in the GRI intake template text field.Preparation for imaging — Dilating drops [one each of 1% tropicamide and 2.5% phenylephrine] are instilled, unless contraindicated or patient refuses permission to instil drops, and the patient waits for 15 min or until the pupil diameters are at least 4 mm. We use the waiting time of 15 min to discuss the appearance of a normal retinal and the value of retinal imaging as a window into vascular health. In the absence of pupil dilation and before being imaged the patient requires five minutes [minimum] of dark adaptation in a windowless or pitch black room in order to maximize pupil size.Imaging sequence — a total of 6 images per eye are acquired, two macula-centred [stereo] fields are imaged first for each eye. The disc-centred field is the third field to be imaged [for vessel calibre and disc assessment]. The nasal and superior-temporal fields for documenting diabetic retinopathy and other findings are the fourth and fifth retinal fields, respectively. The sixth field is the anterior eye/external field for documentation of ocular surface and lid pathology and for future patient identification (Fig. 1).Camera maintenance — Procedures for camera start up, close down, lens cleaning, storage and syncing with the GRI application have been documented for use by site staff.

**Fig. 1 Fig1:**
[figure not shown]
Diabetic Retinopathy Screening imaging fieldsKey elements of the diabetic retinopathy grading protocol are as follows —Grading of retinopathy and vessel calibre measurements are being undertaken by Centre for Eye Research Australia [CERA]-certified graders at the Royal Victorian Eye and Ear Hospital, Australia [RVEEH] grading centre, with ophthalmological adjudication as required.Images are first read for presence and extent of retinal pathologic lesions (haemorrhages and microaneurysms, venous beading etc.) i.e. number of specific lesions per retinal quadrant per image per eye are documented electronically according to the Early Treatment Diabetic Retinopathy Study standardised grading protocol. A grading algorithm based on the Early Treatment Diabetic Retinopathy Study [ETDRS] classification of diabetic retinopathy analyses the electronically-entered retinal lesion data automatically calculates a preliminary clinical level of diabetic retinopathy. This initial grading is either accepted or modified by a grader after comparison with the relevant ETDRS standard field.The referral protocol (Fig. 2) is based on the 2008 NHMRC Guidelines for the Management of Diabetic Retinopathy.The reporting protocol (Fig. 3) has been developed with a view to highlighting the essential management recommendation in the TEAMSnet retinopathy screening report that is sent to Communicare at the participating site via Argus messaging (a third party vendor providing secure communications between health services) for the primary care health professional to evaluate and action in the context of the participant’s prior ocular history in the EHR [as is the case with pathology reports].Subsequently, the disc-centred images in a specific format will be used by graders for retinal vessel calibre measurements, which have been shown to predict CVD and retinopathy onset and progression (Fig. 4) [11, 12].

**Fig. 2 Fig2:**
[figure not shown]
Diabetic Retinopathy Screening referral protocol

**Fig. 3 Fig3:**
[figure not shown]
Diabetic Retinopathy Screening reporting protocol

**Fig. 4 Fig4:**
[figure not shown]
Retinal vessels used for calibre measurement protocolSNAPE lifestyle survey development, administration, reporting and referral protocolsValidated surveys for smoking, alcohol, physical activity and emotional wellbeing/depression have been codified into a survey tool for online use via CDMP or mobile tablet login. For offline use a print copy of the SNAPE survey reporting template can be used. A relevant and validated nutrition survey is not available so experienced research nutritionists and clinicians have developed a brief diet quality questionnaire adapted from recent studies in Indigenous health.Trained study staff will administer the suite of surveys during the second study visit some 6- months after the imaging visit. The SNAPE report (Fig. 5) can be viewed either in the EHR systems (within 24 h) or immediately via login to CDMP or the mobile tablet. The primary care clinician upon review of the report will generate a referral as indicated. High depression scores are brought to the immediate attention of the participant’s treating clinician. Participants’ comments around goals and barriers/motivators to change, such as food security (access to healthy food), will be documented by the survey administrator.

